### Sample size calculation

Based on historical data from the Web-based Distress Management Program for Implantable Cardioverter Defibrillator (WEBCARE) patients that evaluated the effectiveness of an online behavioural treatment based on problem-solving principles of cognitive behavioural therapy [47, 48], we assume that a difference in device acceptance, as measured by the Florida Patient Acceptance Survey, of 3 points at 12 months is the minimal clinically relevant difference between treatment groups. We further assume a standard deviation (SD) of 9 points. Targeting the power analysis to these assumptions, with a type I error of 0.05 (two-sided) and a power of 90%, 382 patients need to be evaluable for the primary endpoint. To compensate for loss to follow-up (estimated at 20%), we will aim to randomise a total of 478 patients (239 in each arm).

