### Statistical methods

#### General analyses

Data will be analysed according to the modified intention-to-treat principle (i.e., all patients with a 12-month evaluation will be analysed as randomised). Categorical variables will be summarised as n (%), continuous variables as min-max, mean (SD), and median. All summaries will be reported by randomisation group. Kaplan-Meier models will be used to estimate survival functions related to time-to-event endpoints e.g. mortality, stratified by group. Regression analyses, linear, logistic, and Cox proportional hazard will be used as appropriate. The type of analysis will depend on the endpoint in question. The primary analysis will be a linear regression of patients’ scores on the Florida Patient Acceptance Survey at 12 months including randomisation group, baseline score and strata as factors and patients’ Florida Patient Acceptance Survey scores at baseline as covariates. Potential confounders, apart from baseline and stratification variables, identified by clinical consensus, will be included in multivariable analyses when appropriate (e.g. when performing sub-group analyses). Additionally, a mixed effects model will be used to analyse the longitudinal change in mean device acceptance scores on the Florida Patient Acceptance Survey while adjusting for strata and baseline Florida Patient Acceptance Survey scores, incorporating random effects to model the homogeneity within cluster and the correlation within patient across time.

Subgroup analyses are planned for the primary endpoint with respect to: Type of device (CRT-D versus ICD); symptomatic heart failure (NYHA class I-II (mild) versus NYHA class III-IV (severe)); indication (primary versus secondary prevention); sex (female versus male); age (median split); depression status (PHQ score < 9 versus ≥10). All other subgroup analyses are explorative.

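### The planned age subgroup analysis is a median split, which costs about 36% of the information on effect modification if age is roughly normal and the effect changes linearly with it

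*Protocol article*

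**What the plan says.** Under General analyses, the protocol article introduces a list of six factors with "Subgroup analyses are planned for the primary endpoint with respect to". Device type, indication and sex are natural categories. NYHA class and depression score have their limits printed. Age appears as "age (median split": the cut is whatever the observed median turns out to be. The list closes with "All other subgroup analyses are explorative".

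The same section fixes the primary model: "The primary analysis will be a linear regression of patients’ scores on the Florida Patient Acceptance Survey at 12 months". It names no test of effect modification and does not mention age as a continuous modifier. The closing paragraph of the cost-effectiveness analyses section leaves details to a statistical analysis plan, which is not shown, to be written before the data are released.

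**The concern.** Age is measured on a continuous scale. Cutting it at the median treats everyone in a half as alike and separates patients who sit just either side of the cut. If benefit rises or falls steadily with age, most of that signal lies in the contrast between the youngest and oldest patients, and the split blurs it.

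The trial is sized for the main effect, so interaction tests start with little power. A further loss makes it more likely that real variation with age is reported as no evidence of variation. That is a practical question for an intervention delivered by app and website. And because the article labels analyses outside its list as explorative, a continuous-age analysis added later would, as written, rank below the split.

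**Working it through.** **Inputs.** From Sample size calculation: a difference "of 3 points at 12 months is the minimal clinically relevant difference between treatment groups"; "We further assume a standard deviation (SD) of 9 points"; and "with a type I error of 0.05 (two-sided) and a power of 90%, 382 patients need to be evaluable for the primary endpoint". Loss to follow-up is put at 20%. Allocation is 1:1. The age distribution and the shape of any interaction are not in the documents and are assumed below.

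**The plan's own figure.** The normal approximation is n per arm = 2 × (1.960 + 1.282)² × 9²/3² = 189.1, rounded up to 190, or 380 in total. The t-based version gives 190.1, rounded up to 191, or 382. Then 382/0.8 = 477.5, rounded up to 478. The stated 382 and 478 are reproduced.

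**Information kept by the split.** For an effect linear in age, the efficiency of the split relative to continuous age is the squared correlation between age and the indicator of being above the median. For normal age this is 2/π = 0.637, a loss of 36%; 0.637 × 382 = 243. Other assumed shapes:

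| Assumed age distribution | Information lost | 382 patients act like |
|---|---|---|
| Uniform | 25% | 287 |
| Normal (mean 62, SD 12), truncated to 18–85 years | 34% | 251 |
| Moderately left-skewed | 35–38% | 249–239 |
| Normal | 36% | 243 |
| Strongly left-skewed | 41–45% | 227–211 |

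**What this does to power.** With age in SD units, the standard error of the continuous interaction slope is 2 × 9/√382 = 0.921 points. The slope with 80% power is (1.960 + 0.842) × 0.921 = 2.58 points per SD of age. After the split, the two halves differ in mean age by 2 × √(2/π) = 1.596 SD, so their treatment effects differ by 2.58 × 1.596 = 4.12 points. With 382/4 = 95.5 patients per cell, the standard error of that difference is 9 × √(4/95.5) = 1.84. Power is Φ(4.12/1.84 − 1.960), about 61%. Simulation with 382 patients, normal age and SD 9 (3,000 runs) gave 79.1% continuous and 60.9% split. For uniform age it gave 79.6% and 66.6%. At 45% loss (efficiency 0.553) the formula gives Φ(2.802 × √0.553 − 1.960) = 55%.

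**Other interaction sizes, normal age, same formula.**

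- 90% power on continuous age falls to Φ(3.242 × √0.637 − 1.960) = 73%.
- A 3-point difference between halves, equal to the whole design difference, has power Φ(3/1.84 − 1.960) = 37% with the split. The matching slope is 3/1.596 = 1.88 points per SD, and on continuous age its power is Φ(1.88/0.921 − 1.960) = 53%.
- A slope of 0.9 points per SD has about 16% power continuous and 12% split.

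**When the split is better.** If the true effect is a step at the median, the split loses nothing. The same squared correlation then counts against the linear term.

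**The case against.** The strongest reply is that a median split is a legitimate prespecified rule. It is set on a baseline variable without sight of outcomes and gives two groups of equal size, which a fixed age might not. The article does not exclude a continuous term, and the unseen analysis plan may contain one. Most of this stands. What remains is that the article chooses the form of the planned age analysis and puts other subgroup analyses in the explorative class. This is therefore a stated choice that can be improved, not a detail left open.

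It is also fair to say that the trial's size is the main limit. The 80% example needs a 4.1-point difference between age halves, more than the 3-point design difference. For small interactions both tests are nearly uninformative.

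A reader might infer several stronger things that the documents do not support:

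- **That a third of the information is lost as a matter of fact.** The figure depends on an age distribution and an interaction shape that the documents do not give.
- **That a cut known only after recruitment lets results be chosen or inflates false positives.** The rule is fixed in advance, so it does not.
- **That the cut has no clinical meaning, or prevents comparison with other trials.** The article merely gives no rationale, and no other trial's age analysis is described.

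**Conclusion.** The point holds in a limited, conditional form. The planned age analysis uses a less efficient method than the primary model readily allows. If the effect changes about linearly with age, the loss is about 36% for normal age and 25–45% over the shapes tried, taking an 80% chance of detection down to about 61% (55–68% over the same shapes). The upper end follows from efficiency 0.75: Φ(2.802 × √0.75 − 1.960) = 68%. These power figures further assume a residual SD of 9, 382 evaluable patients, and that the age subgroups are compared by an interaction test.

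The consequence is confined to one of six planned subgroup analyses. Type I error, the primary analysis and the sample size are not affected, and no conclusion of the trial is tied to this subgroup. It is a worthwhile refinement, not an error.

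**What to change.** In the statistical analysis plan, before data release, define the planned test of effect modification by age as the arm-by-age interaction with age continuous and linear, added with the age main effect to the primary regression of the 12-month score. Prespecify a spline version as a check for non-linearity. State that this is the planned age analysis, so that it is not read as explorative, and keep the median split only for descriptive tables or the forest plot.

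The cost is about one line of text, with no extra data and no change in sample size. The small downside is reliance on linearity: a linear term can miss a step or a curved pattern. The spline check is there to show this, though its own power will be limited at this sample size.

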#### Cost-effectiveness analyses

The analysis of resource use and costs will be conducted on individual participants’ aggregated cost measures during the observation period (12/24 months) from the inclusion date for each individual participant. Cost data are usually skewed and therefore require special analytical methods. The analysis will use the current standard methodology for cost data (generalised regression assuming logistic link function and residuals with gamma distribution). Other methods will be explored to identify the specifications that provide better fit to the data.

All-cause mortality, survival time, retirement and time to retirement will be estimated from inclusion date until death or censoring using appropriate statistical models (Cox-regression or similar). All-cause and cardiac-related mortality will also be used as measures of effect in the cost-effectiveness analysis.

Quality-adjusted life years (QALYs) will be estimated for each individual participant using all the available data points from the EQ-VAS and EQ-5D instrument. The EQ-5D scores will be converted to utility measures (index ranging from 0 to 1) using the recommended algorithm. Work is currently in progress to establish an updated Danish value set. The analysis will be based on the most updated value set at the time of analysis. Sensitivity analysis will be conducted using different value sets. The QALYs will include the area “under the curve” of the different data points during the observation period or until death.

The cost-effectiveness/cost-utility analysis generates results in terms of incremental cost-effectiveness ratios (ICERs). This analysis will use the data set of individual participants’ monitarised resource use (cost) and QALY. Mixed level difference-in-difference modelling will identify the average incremental cost and effect of the intervention in comparison with the control group (the ICER). By assuming a society treshold value for health benefits (QALYs), the net monetary value of the intervention will be analysed for the whole study population (intention-to-treat and per-protocol) and subgroups of the population. In order to assess the precision, the ICERs sensitivity analysis (relating to structural uncertainty) and bootstrapping methods (relating to statistical/parameter uncertainty) will be performed. Both a short-term and a long-term cost-effectiveness analysis (CEA) will be performed. The short-term CEA will use 12/24 months’ time horizon (equivalent to the two-year follow-up period) based on the data obtained through the trial. The long-term CEA will have a lifetime time horizon and will employ a purpose-built model of health outcomes and resource use. The model will extend both cost and effect data obtained from the trial using appropriate statistical methods. Analyses of the CEA will include probabilistic analyses, sensitivity analyses, and scenario analyses. The main cost-effectiveness results will be described as the incremental cost per QALY gained and net-monetary benefit.

Before release of the data for analyses, the statistician involved in the project will write a detailed statistical analysis plan that will be subject to review and approval by the steering committee. Data will be analysed using STATA and R via OPEN Analyse, which is an analysis environment (platform), where data can be stored and processed securely on a server, which is in compliance with the General Data Protection Regulation Directive 95/46/EC.

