#### Cost-effectiveness

In order to assess the effectiveness of the care innovation, a cost-effectiveness/cost-utility analysis will be performed, estimating the incremental costs and effects of the ACQUIRE-ICD care innovation and comparing the two arms. The effect, in terms of changed/improved health status/QoL (i.e., Quality Adjusted Life Years), will be estimated using the EQ-5D. Patients will fill in the EQ-5D questionnaire and the associated VAS at different points in time (at inclusion, at 6-, 12-, and 24-months of follow up). The EQ-5D is a standardised instrument for use as a measure of health outcome developed by health economists for this purpose. The measure consists of a VAS, with patients rating their health on a scale from 0 (worst imaginable health status) to 100 (best imaginable health status), and a descriptive system comprising five questions assessing the following domains: Mobility, self-care, usual activities, pain/discomfort, and anxiety/depression [35]. Each question can be scored as: having no problems (level 1), slight problems (level 2), moderate problems (level 3), severe problems (level 4), and extreme problems (level 5). Subsequently, it is possible to estimate a utility score, a single summary index derived on the basis of the EQ-5D domains, with this information being useful in cost-utility analysis.

Resource use and costs relating to the ACQUIRE-ICD care innovation will be obtained prospectively as costs related to individual participants (variable costs) and the program (fixed costs). Healthcare resource use will be analysed based on data extraction from national health registries for individual participants. The costing period will be from the day of entry into the trial and 12/24 months post implantation. Resource data will include services used in the hospital sector (National Patient Registry – somatic and psychiatry inpatient and outpatient contacts, the Primary Care Registry and Registry of Prescription Medication provided by the primary pharmacies). These resources will be valued using current unit costs (converted to €) based on national sources using tariffs for diagnostic related groups (hospital service), reimbursement fees (primary care service), transaction costs (pharmaceutical services), current salaries, project accounts and expert assessment.

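### The cost regression is specified with a logistic link, which holds mean cost below €1, so it cannot be fitted to euro costs as written; a log link is needed.

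*Protocol article*

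**What the plan says.** All references are to the protocol article.

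- **Outcome.** Under Statistical methods, Cost-effectiveness analyses, resource use and costs are analysed on "individual participants’ aggregated cost measures during the observation period (12/24 months"). Intervention cost and healthcare cost are both listed as secondary outcomes in Table 1.
- **Scale.** Under Measures, Cost-effectiveness: "These resources will be valued using current unit costs (converted to" euros). Nothing in the article rescales these amounts to a 0–1 range.
- **Reason for a special model.** "Cost data are usually skewed and therefore require special analytical methods".
- **Model.** The article names a "generalised regression assuming logistic link function and residuals with gamma distribution" and describes it as the present standard for cost data.
- **Fallback.** "Other methods will be explored to identify the specifications that provide better fit to the data".
- **Incremental cost.** Later in the same section, mixed-level difference-in-difference modelling is given the job of estimating the average incremental cost and effect, and hence the ICER. The article does not say how that model relates to the gamma regression.

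**The concern.** The link function decides which values the modelled mean can take. A logistic link suits a proportion, because it keeps the mean between 0 and 1. A cost per participant in euros is positive and has no upper bound. A log link keeps the mean positive without capping it, and it is the usual partner of the gamma distribution for skewed costs.

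At stake is whether the stated analysis of a listed secondary outcome can be carried out at all. If the named model cannot be fitted, the cost model is in effect chosen after the data are seen, by way of the sentence on exploring other methods. The protocol would then no longer fix the base specification it appears to fix.

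**Working it through.** The article attaches no figure to the cost model, so there is nothing of its own to reproduce on this point. Its sample size (382 evaluable, 478 randomised) does not depend on the cost model.

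**Inputs.** Logistic link and gamma distribution (Cost-effectiveness analyses); outcome is aggregated cost per participant (same section); unit is the euro (Measures, Cost-effectiveness).

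**Step 1: range of the mean.** Write η for the linear predictor.

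| η | Logistic link, μ = 1/(1+exp(−η)) | Log link, μ = exp(η) |
|---|---|---|
| 0 | 0.5 | 1 |
| 5 | 0.9933 | 148.4 |
| 10 | 0.99995 | 22,026 |
| 30 | 1 to twelve decimal places | about 1.07 × 10¹³ |

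Under the logistic link no value of η takes the mean to €1 or beyond.

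**Step 2: does a best fit exist within that range?** For one observation y, the gamma log-likelihood depends on μ through −(y/μ + log μ). Its derivative in μ is

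y/μ² − 1/μ = (y − μ)/μ².

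Summed over the n participants of one arm with observed mean ȳ, this is n(ȳ − μ)/μ². It is positive for every μ < ȳ. The link allows only μ < 1. So if ȳ is above 1, the likelihood rises over the whole permitted range, and its upper limit is approached only as μ → 1, that is, as η → ∞. No finite maximum-likelihood estimate exists.

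**Step 3: consequence for the arm comparison.** When both arm means exceed €1, both fitted means are pushed to the same bound of 1. The fitted cost difference goes to zero whatever the true difference is, and the coefficients do not settle.

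**Step 4: software check.** Assumptions not in the article: simulated gamma costs with a mean of about €10,000, shape 1 and 239 per arm. Python statsmodels refuses gamma with a logit link as invalid for the family. Gamma with a log link converges and returns the two arm means, €10,030 and €10,853. This is illustration only. The refusal is a check against a list of permitted links. A model with only an intercept and an arm term is saturated, so any workable link would return the arm means. The evidence is steps 1 to 3, which hold for any arm mean cost above €1.

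**The case against.** **It is only a slip for log.** Very probably. The gamma distribution, the reference to skewness and the claim to follow standard practice all point that way. The error also shows itself, because software will not fit the combination, so a wrong published result is unlikely. That limits the harm but leaves the text wrong. Elsewhere the article uses logistic in its ordinary sense, for regression analyses in General analyses and for labour-market outcomes under Measures, so a reader cannot simply assume a different meaning here.

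**The article already allows for correction.** It plans to explore alternatives for better fit, and it requires a detailed statistical analysis plan, approved by the steering committee, before data are released. Both reduce the practical risk. Neither corrects the base model, and a search for better fit presupposes a base model that can be fitted.

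**A charitable reading could rescue the wording.** A reader might suppose that costs are scaled to 0–1, or that a logistic part handles any versus no cost and a gamma part handles the amount. The article describes neither. It names one regression with one link.

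**A stronger reading is tempting.** A reader might infer that the numerator of the ICER and the net monetary benefit are invalid because they rest on this regression. The article does not support that. It assigns incremental cost and effect to the mixed-level difference-in-difference model and does not say that the gamma regression feeds it. What can be said is that the relation between the two is left unstated.

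**Conclusion.** The point stands as a specification error in a secondary analysis. As written, the regression for aggregated euro costs has no finite fit for any arm mean above €1, so it cannot be run, and it is not the standard cost model the article says it is. The only assumptions are that logistic link has its usual meaning and that costs are analysed in euros, as stated; no particular cost level is needed.

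The reach is limited to the analysis of resource use and costs. The primary endpoint, its linear regression and the sample size are unaffected. Damage to the ICER or to net monetary benefit is not shown.

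**What to change.** 1. In Statistical methods, Cost-effectiveness analyses, change the link from logistic to log and keep the gamma distribution.
2. Add one sentence saying how this cost regression relates to the mixed-level difference-in-difference model used for incremental cost and the ICER: whether it is a separate descriptive analysis of costs or supplies the cost side of that model.

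The cost is one word and one sentence, carried into the statistical analysis plan before data release. No patients, data items or visits change.

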#### Comprehensive interactive ACQUIRE-ICD eHealth intervention

The ACQUIRE-ICD eHealth intervention is delivered via the Liva Healthcare platform, which was developed to help patients manage chronic diseases: https://livahealthcare.com/the-platform/. Liva is browser-based for the health care professionals, with access to the platform and its tools for patients via native solutions for smartphone (IOS and Android), tablet / iPad, or a website application. The platform makes it possible for patients, health care professionals and other stakeholders to access, monitor and update personal health data in a secure ISO 27001 environment. It allows for patients to write personal messages to health care professionals and vice versa, to set targets for behavioural change, to receive push messages to remind them to monitor lifestyle and complete questionnaires, take action if targets are not met, to engage in dialogues with fellow patients (via the platform’s forum), and for health care professionals to support patients with positive reinforcement and multi-media contents (vodcasts, pdf-files, etc.), so that patients can reach their goals [36].

The intervention consists of various components and lasts 12 months. An overview of the components is provided in Table 3 and a more detailed description is provided below.

**Table 3 Tab3:** Overview of the components of the ACQUIRE-ICD intervention

• Goal-setting for behavioral change • Monthly patient and clinician tracking and monitoring of symptoms of depression (PHQ-8), anxiety (GAD-7) and health status (EQ-VAS) and feedback • Referral for psychological treatment based on value-based cognitive behavioral therapy [*only for patients with a positive screen on depression and/or anxiety*] • Dialogues with nursing staff via the platform [*1–3 months post implant: once a week; 4–12 months: once a month; potential to obtain extra feedback*] • Information provision and education (e.g. on ICD-related topics, anxiety, depression, relaxation training, by means of multi-media contents, such as quizzes, vodcasts of patients and health care professionals, etc.) [examples of vodcasts are available here: https://helbredsprofilen.dk/en] • Forum with online community network with *“patients like me”*	

*EQ-VAS* EuroQoL visual analogue scale, *GAD* Generalised Anxiety Disorder scale, *PHQ* Patient Health Questionnaire

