##### Completion and monitoring of symptoms of depression and anxiety and health status

Depression and anxiety symptom and health status monitoring was included in the intervention to educate patients about their physical and mental health, as symptoms of depression and anxiety may serve as a barrier to behaviour change and compliance. Without this awareness, patients’ endeavours to change are likely to fail, which may decrease their motivation on the long-term, and influence their QoL and successful disease management. Patients themselves indicate that psychological status is one of the primary reasons for hospital readmission, with unexpectedly few patients pointing to non-compliance as the culprit [31]. Poor QoL and poor patient-rated health status have been shown to predict poor prognosis and mortality in patients with an ICD, despite state-of-the-art treatment [38].

Patients will receive automatic prompts once a month to complete the Patient Health Questionnaire (PHQ-8) [39], the Generalised Anxiety Disorder scale (GAD-7) [40], and the EuroQol visual analogue scale (EQ-VAS) [41] to monitor their symptoms of depression and anxiety and health status, respectively. We chose to use the 8-item version of the PHQ rather than the 9-item version, removing the item on suicidal ideation, as it is not an accurate suicide screen and few cardiac patients endorse this item [39]. The core symptoms of depression as assessed with the PHQ-2 or PHQ-9 predict new onset myocardial infarction and mortality [42]. Following completion of the questionnaires via the platform, the scores are plotted into a graph and added to previously completed scores to generate a graphic summary showing the evolution of scores over time. This allows patients and nursing staff to routinely track patients’ status, flag deteriorations early on that serve as cues for timely action for patients and the ICD care team to discuss whether action needs to be taken. An automatic reminder system is in place if patients do not complete the questionnaires. Prior to the ACQUIRE-ICD trial, we evaluated the experiences of patients and nursing staff with health status monitoring in a feasibility study of patients with health failure. Although not all patients were positive about monitoring, several patients and the nursing staff found it a useful tool and felt that it provided a more true picture of how patients felt [43].

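### The QALY rule admits every available EQ-VAS and EQ-5D reading, so monthly EQ-VAS scores collected in the intervention arm only could enter the comparison of arms

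*Protocol article*

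**What the plan says.** The statistical section on cost-effectiveness estimates QALYs for each participant "using all the available data points from the EQ-VAS and EQ-5D instrument". The QALY is the area under the curve "of the different data points during the observation period or until death". The same paragraph gives one conversion to utility, and only for one of the two instruments: "The EQ-5D scores will be converted to utility measures (index ranging from 0 to 1) using the recommended algorithm".

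Two data streams contain the EQ-VAS:

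- **Trial assessments.** The Measures section on cost-effectiveness schedules the EQ-5D and its VAS "at inclusion, at 6-, 12-, and 24-months of follow up". The QALY row of Table 2 lists the EQ-5D-5L plus VAS at the same four times, and the table footnote applies all measures to both arms.
- **Platform monitoring.** Table 3 makes monthly tracking of depression, "anxiety (GAD-7) and health status (EQ-VAS) and feedback" a component of the intervention, which lasts 12 months. The section on symptom monitoring describes the monthly prompts. The usual care section describes no such monitoring.

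The article does not say whether the platform scores count as available data for the QALY.

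**The concern.** A QALY computed as an area under the curve depends on when health is measured as well as on health itself. With the same measurement times in both arms, interpolation error is the same for identical health courses and cancels in the difference. With monthly readings in one arm and six-monthly readings in the other, it does not cancel, and a QALY difference can appear where there is no effect.

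The monthly scores are also part of the treatment. Nurses respond each time the questionnaires are completed, and a fall of 10 or more EQ-VAS points leads them to ask the patient to reflect on the reasons. Such scores are not neutral outcome measurements.

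A second problem does not depend on the platform. The EQ-VAS is a 0-100 self-rating, whereas the utility index comes from the EQ-5D descriptive system. The rule names both as inputs without saying how they combine.

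The incremental cost per QALY gained and the net monetary benefit are the main cost-effectiveness results, so any artefact in the QALY difference passes directly into them.

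**Working it through.** The article gives no QALY figure to reproduce, and no health trajectory or threshold value. The visit times below come from the article; all health values are assumptions.

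**1. Readings by arm in the first 12 months**

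| Stream | Months | Arms |
|---|---|---|
| EQ-5D-5L + VAS (Table 2) | 0, 6, 12 | both |
| Platform EQ-VAS (Table 3) | monthly | intervention only |

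Months 6 and 12 coincide with trial visits, so the platform adds 12 − 2 = 10 time points. After month 12 both arms have only the 24-month assessment, so any 12-month discrepancy carries unchanged to 24 months.

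**2. Formula.** QALY = Σ [(t₍ᵢ₊₁₎ − tᵢ)/12] × (uᵢ + u₍ᵢ₊₁₎)/2, with t in months. The course is identical in both arms, so the true difference is 0. Monthly EQ-VAS values are treated as if they were utilities and fully completed.

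**3. Rise of d over two months, then level.** Shortfall from the plateau over 12 months:

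- Months 0/6/12: d × (6/12)/2 = 0.250d
- Monthly: d × (2/12)/2 = 0.083d
- Spurious gain for the intervention arm: 0.250d − 0.083d = 0.167d

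This is 0.008 for d = 0.05, 0.017 for d = 0.10 and 0.025 for d = 0.15. At an assumed EUR 30,000 per QALY, the range is EUR 250 to 750 per patient.

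**4. Smooth recovery.** u(t) = 0.75 − d·exp(−t/τ). Monthly area minus 0/6/12 area:

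| d | τ = 1 month | τ = 2 | τ = 3 | τ = 6 |
|---|---|---|---|---|
| 0.05 | 0.0081 | 0.0053 | 0.0037 | 0.0017 |
| 0.10 | 0.0161 | 0.0106 | 0.0075 | 0.0034 |
| 0.15 | 0.0242 | 0.0159 | 0.0112 | 0.0052 |

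For d = 0.10 and τ = 2, the areas are 0.7330 (monthly) and 0.7224 (0/6/12).

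**5. Other shapes**

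- Transient dip, u(t) = 0.75 − d·exp(−((t − 3)/1.5)²): −0.010 for d = 0.05 and −0.021 for d = 0.10.
- Linear course: 0.

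**6. Mixing the two scales in one curve.** Take a flat index of 0.80 at months 0, 6 and 12, with rescaled VAS values lower by an offset at the other ten months. The intervention arm shifts by −(10/12) × offset. That is −0.042, −0.083 and −0.125 QALY for assumed offsets of 0.05, 0.10 and 0.15. A VAS above the index would give the opposite sign.

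**7. Shared visits only.** Identical courses measured at the same times give a difference of exactly 0.

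**The case against.** The strongest reply is that the rule was never meant to reach the platform data. Table 2 ties the QALY to four assessments in both arms, and the Measures section says that QALYs are estimated with the EQ-5D. Monthly monitoring is described throughout as a care tool and nowhere as a source of economic data. On this reading, the available data points are whichever of the four scheduled assessments a participant completed. A QALY built on the EQ-5D index has the same schedule in both arms and is unaffected. The article also promises a detailed statistical analysis plan before data release, and the quantity is a secondary, economic one.

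Much of this stands. A reader might infer that the arms' areas will differ by schedule alone. The documents do not support that: no section brings platform scores into the QALY, a linear course produces no difference, and the sign depends on the trajectory.

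The reply does not remove the point. The sentence is a positive rule rather than an omission, and an analysis plan that follows it literally inherits the problem. Nor is the EQ-VAS a stray word there, since Table 2 also lists the VAS under QALY. Even at the four shared visits, no route from EQ-VAS to utility is given.

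**Conclusion.** The point holds as a badly fixed rule with a possible bias, not an established one. A schedule-only difference requires that platform EQ-VAS scores be counted as available, that they be placed on a utility scale, and that health change non-linearly between the shared visits. If all three hold, the spurious difference is 0.008 to 0.025 QALY in favour of the intervention for a two-month recovery of 0.05 to 0.15. It is 0.002 to 0.024 for smoother recoveries of the same size, and −0.010 to −0.021 for a dip of 0.05 to 0.10 around month 3. All these trajectories are assumed. Putting VAS and index values into one curve could shift the result further, by an amount that depends on an offset the article does not give.

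The lack of a stated conversion for the EQ-VAS needs none of these conditions. A reader might also infer from the phrase "index ranging from 0 to 1" that negative index values are to be cut off at 0, but the article orders no truncation, and that inference forms no part of this point. The primary endpoint and the sample size are not affected.

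**What to change.** In the Cost-effectiveness analyses section, replace the rule on data points with three statements:

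- QALYs are calculated only from the EQ-5D-5L index at 0, 6, 12 and 24 months, in both arms.
- EQ-VAS from those four assessments is reported separately.
- Monthly EQ-VAS collected on the platform does not enter the QALY.

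This is a short wording change, needs no new data, and agrees with the schedule already in Table 2. The small cost is that the monthly readings go unused in the QALY. The change removes the schedule-only difference. It does not remove the interpolation error of a six-monthly schedule when the arms' courses differ in shape, but monthly readings in one arm would not solve that either.
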